## Methods

### Patient and public involvement

Participants in previous pilot studies were consulted regarding their satisfaction with the exercise intervention and the characteristics of the exercise professionals.^16^ These inputs have been used to improve the quality of the interventions. Medical doctors from participating hospitals will collaborate with the research group in recruiting participants, disseminating research findings through publications and seminars and delivering relevant educational content.

### Trial design

This is a multicentre, two-arm, parallel-group, randomised controlled trial (RCT) with a 1:1 allocation ratio and an equivalence framework. Pregnant women will be randomly assigned to either an IN or ON supervised multicomponent exercise intervention.

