We hypothesised that a multicomponent supervised prenatal physical exercise programme previously described in Santos-Rocha *et al*’s study^14^ positively impacts PA, fitness, lifestyle and health parameters of women throughout pregnancy, regardless of the delivery environment (in-person (IN) *vs* online (ON)), maternal age or weekly volume of PA, and that both exercise environments are equally effective.

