### Statistical methods for primary and secondary outcomes

Demographic data (age, weight, gestational age, area of residence and date of birth) will be described using frequencies and percentages for categorical variables.

Descriptive statistics (mean, SD, median and IQR) will be used to summarise baseline characteristics of participants in both groups (IN and ON).

Descriptive and inferential statistics will be applied to all outcomes.

A comparative analysis of IN *versus* ON interventions will be conducted using both intention-to-treat and per-protocol approaches. Comparative analysis will be used to compare changes in primary and secondary outcomes between IN and ON groups over time (baseline and postintervention). Subgroup analyses will evaluate potential differences between maternal age groups (<35 *vs* 35+ years) and PA level groups.

Adherence to the intervention (proportion of attendance in the planned sessions) will be calculated after the postintervention assessments.

Data from participants who do not complete at least 80% of the scheduled sessions will be considered a loss to follow-up.

Regarding additional outcome analysis, the evaluation of interventions and resources will be performed through descriptive analysis, summarising satisfaction with resources and exercise interventions.

Continuous variables will be assessed for normality using Shapiro–Wilk tests. Normally distributed variables will be presented as mean±SD and analysed using the independent sample t-test. The non-normally distributed data will be reported as the median with IQR and will be analysed using the Mann–Whitney test. For the within-group difference, normally distributed variables will be calculated with the paired-sample t-test. In contrast, those non-normally distributed variables will be calculated with the paired-sample non-parametric Wilcoxon test. Categorical data will be analysed using Pearson’s χ^2^ test or Fisher’s exact test, as appropriate.

A significance level of 0.05 (alpha level) will be set for all statistical tests. Power calculations were performed to ensure that the study was adequately powered to detect clinically significant differences between groups. All statistical analyses will be conducted in Statistical Package for the Social Sciences.

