## Discussion

The ACTIVE PREGNANCY trial is an equivalence RCT with two parallel exercise intervention groups based on a multisetting, multicomponent, customised, supervised prenatal exercise programme.

The study is expected to provide evidence on the effectiveness of supervised prenatal exercise programmes delivered IN or ON on PA, fitness, lifestyle and health parameters of pregnant women. The findings will contribute to exercise prescription guidelines, social prescription programmes and policy recommendations aimed at promoting maternal health during pregnancy. Moreover, this study will generate evidence on how to incorporate exercise into everyday life for pregnant women.

Previous studies have investigated the effects of various IN exercise interventions on health outcomes in pregnant women. However, none of these studies have focused primarily on investigating the effect of exercise interventions on actual PA levels and age groups.

The literature is scarce regarding the effects of such interventions on health-related and skill-related fitness components, while numerous non-validated tools are used for fitness assessment.^6^ Moreover, the literature is scarce regarding the effectiveness of virtual interventions on health and fitness parameters. Thus, the main purpose of the ACTIVE PREGNANCY trial is to compare the effect of two different contexts of intervention.

Additionally, the ACTIVE PREGNANCY trial includes a process evaluation of the exercise intervention to enhance adherence. It explores the acceptability of resources promoting active and healthy lifestyles supported by health technology.

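### The trial is declared an equivalence trial, but its stated tests and sample size are built to detect a difference, so they cannot support equivalence

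*Protocol article*

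**What the plan says.** - **Framework.** Trial design calls the study a "randomised controlled trial (RCT) with a 1:1 allocation ratio and an equivalence framework". The Discussion repeats it: "The ACTIVE PREGNANCY trial is an equivalence RCT with two parallel exercise intervention groups".
- **Hypothesis.** The hypothesis closing Background and rationale includes that "both exercise environments are equally effective".
- **Between-arm tests.** Statistical methods for primary and secondary outcomes says: "Normally distributed variables will be presented as mean±SD and analysed using the independent sample t-test". Non-normal variables go to the Mann–Whitney test and categorical ones to Pearson's chi-square or Fisher's exact test. A level of 0.05 applies to every test.
- **Purpose of the power calculation.** The same section says power was computed so that clinically significant between-group differences could be detected.
- **Sample size.** One calculation is for a within-group pre–post change (36 women). The other gives 59 per group for women in an exercise programme against women who are not. With 20% expected loss, 100 per arm are planned.
- **Analysis sets and looks.** IN and ON are compared by both intention-to-treat (ITT) and per-protocol approaches. Interim analysis schedules a look every 3 months.

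**The concern.** A test of difference takes no difference as its null hypothesis. An equivalence claim needs the reverse: the null is that the arms differ by at least some margin, and the data must reject it. Under the tests the article names, rejection speaks against the hypothesis of equal effectiveness, while non-rejection leaves it unproven. No result of these tests can establish the claim that the framework and hypothesis set up.

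The conflict is in stated text. The article does not merely leave equivalence details for elsewhere. It names the tests, gives their level, and says the trial was sized and powered to find differences. An analysis plan that used equivalence tests would have to overrule those sentences.

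At stake is the main inference about online against in-person delivery. Noise and lost data make p>0.05 more likely, so difference tests give no protection against a mistaken impression of similarity.

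**Working it through.** **1. The stated sample size.** The 59 per group cannot be rebuilt from the article, which gives neither the outcome nor the mean and SD used. Solving backwards for a two-sample t-test (two-sided 0.05, power 0.80), 59 per group corresponds to a standardised difference of d = 0.52. The normal approximation agrees: (1.960 + 0.842) × √(2/59) = 0.516. If the test was one-sided, d = 0.46. Either way this is a difference calculation, for a contrast (exercise or none) that the trial does not make.

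**2. Evaluable numbers.** 100 per arm less 20% leaves 100 × 0.8 = 80 per arm. Results for the full 100 are shown as the favourable case.

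**3. How often the planned t-test is non-significant when the arms truly differ.** The article gives no SD for the IN–ON comparison, so true differences d are assumed in SD units of the analysed change from baseline. The test statistic follows a non-central t with 2n − 2 degrees of freedom and non-centrality d√(n/2). The chance of p>0.05 is the probability that it falls between the two critical values.

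| Assumed true difference | Non-centrality, n = 80 | P(p>0.05), n = 80 | P(p>0.05), n = 100 |
|---|---|---|---|
| 0.2 SD | 0.2 × √40 = 1.26 | 76% | 71% |
| 0.3 SD | 1.90 | 53% | 44% |
| 0.4 SD | 2.53 | 29% | 20% |
| 0.5 SD | 3.16 | 12% | 6% |

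**4. What the planned size supports under an equivalence test.** Take two one-sided tests at 5% each (a 90% CI inside ±Δ), a true difference of zero and the normal approximation. With SE = √(2/80) = 0.158 SD, power = 2Φ(Δ/SE − 1.645) − 1.

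- Δ = 0.3 SD: 2Φ(1.897 − 1.645) − 1 = about 20%
- Δ = 0.4 SD: 2Φ(2.530 − 1.645) − 1 = about 62%
- Δ = 0.5 SD: 2Φ(3.162 − 1.645) − 1 = about 87%

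The smallest margin with 80% power is (1.645 + 1.282) × 0.158 = about 0.46 SD. At 2.5% per side it is about 0.51 SD.

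For narrower margins, the numbers needed per arm at 5% per side and 80% power are 108 evaluable (135 recruited) at 0.4 SD and 191 evaluable (239 recruited) at 0.3 SD, with recruitment = evaluable/0.8 rounded up.

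**The case against.** Several points on the other side have force.

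- **No sentence says that p>0.05 will be reported as equal effectiveness.** A reader might infer it, because the named tests leave no other route to the hypothesis. It remains an inference, and the point here is only that framework and tests do not match.
- **A margin or confidence-interval rule may exist elsewhere.** Data management refers to a full protocol, and an article may leave such detail to it. So the absence of a margin is not the fault. What stands is that the article's own tests and power statements point the other way.
- **The trial can still answer a question.** Objectives and the Discussion describe comparing the two modes, and difference tests serve that. It would be too strong to say the analysis answers nothing; what it cannot support is equivalence.
- **The percentages in step 3 are not false-equivalence rates.** Whether 0.2 SD is a real failure depends on the margin. With an assumed margin of 0.5 SD, a true 0.2 SD difference counts as equivalent, and the 5% limit of an equivalence test applies only at or beyond the margin. The figures show only that non-significance is a weak guide to similarity.
- **Women may modify their intervention on request.** One might infer that this draws the arms together under ITT. The discontinuation section does not mention crossing between arms, so no weight is put on this.

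**Conclusion.** The point holds as a contradiction within the article: an equivalence framework and hypothesis on one side, difference tests and a difference-based sample size on the other. It should be resolved before results are seen, because it decides what the trial may conclude.

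Its size can only be illustrated. With 80 evaluable per arm, a true difference of 0.2 to 0.5 SD would be non-significant between 76% and 12% of the time (71% to 6% with 100 per arm). These SD values are assumptions, the loss is taken at the article's 20%, and each figure is for a single continuous outcome tested two-sided.

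A reader might also infer that 200 women are too few. The documents do not support that as a general statement. The planned size suits a margin of about 0.46 SD or wider and falls short for 0.3 or 0.4 SD. Which margin is defensible is not a matter these documents settle.

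**What to change.** 1. **Statistical methods.** Name one primary outcome for the equivalence claim, or give each primary outcome its own justified margin ±Δ in its own units. Table 2 lists ten primary rows on scales such as MET-min/week, a 1–5 Likert scale, mL/kg/min, repetitions and mm, so one margin cannot serve all.
2. **Decision rule.** Report the IN–ON difference with a 90% CI (two one-sided tests at 5%). Declare equivalence only if the interval lies wholly within ±Δ, with ITT and per-protocol results both shown and consistent. State that a non-significant difference test is not evidence of equivalence.
3. **Timing.** Fix the margin before any comparative look, including the 3-monthly interim analyses. Recruitment was due to start in May 2025, so this is pressing.
4. **Power statements.** In Sample size and Statistical methods, replace the difference-based justification with the margin that the planned size supports for IN versus ON: about 0.46 SD or wider for 80% power with 80 evaluable per arm and a true difference of zero.
5. **Alternative.** If no such margin can be justified, remove the equivalence label and the claim of equal effectiveness, and report differences with CIs.

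The cost is wording plus one margin decision per outcome carrying the claim. No new assessments are needed. No extra recruitment is needed if a margin of about 0.46 SD or wider is defensible; a narrower one would need more women. The downside is that some outcomes may end as inconclusive, or that the equivalence claim is given up.

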### Trial setting

The study will be conducted in healthcare and fitness centres across participating hospitals and universities in Portugal.

### Participants

This study aims to include healthy pregnant women (uniparous and multiparous) who, after the first clinical visit and ultrasonically confirmed viable intrauterine pregnancy, will be randomly allocated to one of two groups: exercise intervention delivered IN or ON, after signing an informed consent form.

### Eligibility criteria for participants

Inclusion criteria: pregnant women aged 18–50 years; 13–20 weeks of gestation at recruitment; no absolute contraindications to exercise during pregnancy; attending healthcare services regarding pregnancy and understanding the Portuguese language.

Exclusion criteria: medical conditions contraindicating PA and inability to participate in IN or ON formats.

### Eligibility criteria for exercise professionals who will deliver the interventions

The exercise intervention will be carried out by graduated exercise professionals (EQF level 6 or 7), holders of a BSc, MSc or PhD in Exercise or Sport Sciences, with specialisation in exercise testing and prescription during pregnancy. Exercise professionals will explain the study’s objectives and obtain informed consent before conducting assessments and delivering the exercise intervention.

### Exercise intervention programmes and comparators

The interventions follow international guidelines for PA during pregnancy.^7^,^9^ The exercise programme was designed and validated as a complex intervention and underwent three stages: development, pilot testing and evaluation.^14^ Exercise sessions consist of a combination of aerobic, resistance, stretching, balance, coordination, postural and pelvic floor muscle exercises, using multicomponent activities, such as aerobics, dancing, step, Pilates, bar, chair and resistance exercises using elastic bands, exercise balls, mats, dumbbells or body weight.

Table 1 describes both arms of the exercise intervention in line with the American College of Sports Medicine exercise prescription guidelines.^17^

**Table 1 T1:** Description of both arms of the exercise intervention

Arm 1:IN exercise group	Type of exercise: multicomponent prenatal exercise programme, including aerobic, coordination, strength, stretching, balance, postural and pelvic floor muscle training exercises.Duration and frequency: two sessions of 60 min per week for 12 weeks.Intensity: moderate. According to the Borg scale of perceived exertion, which ranges from 6 to 20, moderate exercise is rated between 13 and 14. Each pregnant woman will rate her perceived exertion on a scale of 6–20.IN supervision: qualified exercise physiologists.Setting: healthcare, university or fitness centres.
Arm 2:ON exercise group	Type of exercise: multicomponent prenatal exercise programme, including aerobic, coordination, strength, stretching, balance, postural and pelvic floor muscle training exercises.Duration and frequency: two sessions of 60 min per week for 12 weeks.Intensity: moderate. According to the Borg scale of perceived exertion, which ranges from 6 to 20, moderate exercise is rated between 13 and 14. Each pregnant woman will rate her perceived exertion on a scale of 6–20.Remote supervision using a virtual platform: qualified exercise physiologists.Setting: home.
	Examples of the exercise programme are continuously updated on the ACTIVE PREGNANCY YouTube channel:@GravidezAtiva-ActivePregnancy(https://www.youtube.com/channel/UC0Vyookwc0mcQ5T70imtoNA/playlists).

IN, in-person; ON, online.

### Additional materials describing the intervention

Additional recommendations to participants include open-access educational materials, such as the ACTIVE PREGNANCY Guide (online supplemental 1), walking, swimming or performing a video session from the ACTIVE PREGNANCY YouTube Channel on other days of the week.

Exercise physiologists delivering the intervention will be supported by a specific textbook^18^ and the ACTIVE PREGNANCY YouTube Channel regarding programme planning, exercise testing and prescription and exercise adaptations.

Healthcare professionals providing health screenings and recruiting participants will be supported by the Health Professionals Guide (online supplemental 2).

Individual reports will be provided for each participant and her healthcare provider.

### Explanation for the choice of comparators

Despite the existing evidence on prenatal exercise, there is a need for robust, multicentre studies evaluating the impact of both IN and ON exercise interventions on maternal PA, fitness and health outcomes, independent of maternal age, health status or baseline fitness.

### Criteria for discontinuing or modifying allocated interventions

Participants will be free to discontinue or modify allocated interventions on request or due to medical reasons without any consequences.

### Strategies to improve adherence to interventions

Exercise professionals will monitor adherence to the intervention by recording the number of sessions attended over 12 weeks. Motivational strategies include organising online group meetings, sending weekly WhatsApp and Instagram reminders, providing access to resources promoting an active and healthy lifestyle and offering access to the YouTube channel.

The overall focus of these sessions is based on what already motivates participants to increase or maintain their PA level and healthy lifestyle. This is achieved by fostering interaction among participants to create meaningful group processes, such as support, experience exchange and reflection, as well as collecting feedback regarding the exercise programme and resources. All monthly online sessions will last 20–30 min and are led by exercise and health professionals. These sessions aim: (1) to inform about PA guidelines, benefits associated with PA and possible ways to increase PA during pregnancy; (2) to discuss participant’s barriers, wishes, needs, knowledge and former PA experiences to identify individual characteristics and motivation towards a more physically active lifestyle; (3) to teach the advantages of using a PA tracker, aside from measuring the PA level, the activity trackers are also used as an intervention element to motivate the participants to increase their PA levels, share it on a Strava group and provide feedback on recent PA performances; (4) to collect feedback regarding the organisation of the exercise programme and (5) to discuss other relevant topics chosen by the participants, such as myths about pregnancy PA, postpartum PA, the pelvic floor, uterine contractions, abdominal muscles and diastasis recti, birth, etc.

Individual sessions will be scheduled during the daytime at a time that is as convenient as possible for the participant.

The primary objectives of these motivational strategies are to enhance participant retention and adherence to follow-up, as well as to incorporate a patient-centred approach into the exercise intervention.

### Concomitant care permitted or prohibited during the trial

During the exercise trial, participants will be permitted to continue their routine medical care, including medications and consultations with their primary healthcare providers, as well as maintain their usual PA and nutritional habits, such as participation in other organised exercise programmes or specific sports.

### Timeline

The schematic diagram of the study, including the schedule of enrolment, data collection points (assessments) at baseline (13–20 gestational weeks) and postintervention (25–32 gestational weeks), interventions and additional collection points, is shown in figures1  2.

**Figure 1 F1:**
[figure not shown]
Study’s timeline.

**Figure 2 F2:**
[figure not shown]
Schedule of enrolment, interventions and assessments. −t1, enrolment week; t0, allocation and baseline week; t1, pretraining assessment; t3, post-training assessment (week 12).

### Outcomes

Primary, secondary and additional outcome measures, including the specific measurement variables, timeframe and instruments, are shown in table 2.

**Table 2 T2:** Primary, secondary and additional outcome measures, including the specific measurement variables, timeframe and instruments

Outcome measures	Instruments
Primary outcome measuresTimeframe: baseline (week 0) and after 12-week intervention (weeks 13 and 14)Analysis metric: change from baseline	
PA level and pattern of PA in the type of PA (work, active commuting, exercise, etc.), type of exercise, duration of each session (time spent in PA), weekly frequency and intensity and weekly volume (MET-min/week).	PPAQ^21^ and get active questionnaire for pregnancy^22^
Self-perceived fitness: self-perceived global fitness and fitness components (cardiorespiratory, strength, speed/agility and flexibility) when compared with other women of the same age. Likert scale 1 (poor) to 5 (very good).	IFIS^23^
Cardiorespiratory fitness estimated in mL/kg/min	Cardiorespiratory fitness—6-min walk test (average distance covered in metres and estimated cardiorespiratory fitness in mL/kg/min)^24^https://youtu.be/CUaFgfdSObc
Upper limbs strength	Upper limb strength—wall push-ups (number of repetitions in 30 s)^6 17^https://youtu.be/dp_tRoyxVYU
Lower limbs strength	Lower limb strength—sit-and-stand (number of repetitions in 30 s)^6 17 25^https://youtu.be/3ihcqnzyTXk
Dynamic balance	Dynamic balance—superwoman^6 17^https://youtu.be/Xiv_vWpe4-A
Static balance	Static balance—one-leg stance^6 17^https://youtu.be/sr0eYCfbLiM
Lower limbs flexibility	Lower limbs flexibility—modified sit and reach (mm)^6 17^https://youtu.be/Y6y_FAa3ulk
Upper limbs flexibility	Upper limbs flexibility—back scratch (mm)^6 17^https://youtu.be/MBwKi8kSFx8
Agility	Agility—time up and go over 3-m distance (in min)^6 17^https://youtu.be/3C944cMuTFo
Secondary outcome measuresTimeframe: baseline (week 0) and after 12-week intervention (weeks 13 and 14)Analysis metric: change from baseline	
Sleep quality	PSQI^26^
Weight prepregnancy, weight at baseline and weight gain (kg)	Body weight: measure with the participant wearing light clothing and without shoes^27^
Happiness scale	SHS^28^
Depression scale	EPDS^29^
Adherence to the Mediterranean diet	MEDAS^30^
HR	Measured rest HR, estimated maximal HR and calculated target HR (beats per minute)
Prevalence of pregnancy-related symptoms and health parameters (eg, weight gain, blood pressure, prevalence of gestational diabetes or hypertension and contraindications for PA)	Medical records, pregnancy symptoms inventory and get active questionnaire for pregnancy^22^
Other prespecified outcome measuresTimeframe: after the intervention (13 and 14 weeks)	
Participant satisfaction with the available resources—Likert scale (1–5, with 1 not satisfied at all, and 5 highly satisfied).	Satisfaction with educational digital resources (ie, ACTIVE PREGNANCY Guide, YouTube channel ACTIVE PREGNANCY and the framework of the ACTIVE PREGNANCY app).
Participant satisfaction with the intervention—Likert scale (1–5, with 1 not satisfied at all, and 5 highly satisfied).	A questionnaire explicitly made for the intervention evaluating different domains: type of exercises, hardness of the sessions, difficulty in particular exercises, weekly frequency, duration of the sessions, context of intervention (online, outdoor, gym and hospital), satisfaction with the exercise physiologist, willingness to continue in postpartum, willingness to repeat in future pregnancy and overall satisfaction to be included in the programme.
Feasibility and adherence	Feasibility evaluation of the implementation of the exercise programme: (1) number of women who declined to participate in the study; (2) number of women who gave up participation in the study; (3) adherence to the programme (number of days of actual performance of the exercise programme while admitted) and (4) number of women who completed at least 80% of the study.

EPDS, Edinburgh postpartum depression scale; HR, heart rate; IFIS, International Fitness Scale; MEDAS, Mediterranean Diet Adherence Screener; MET, metabolic equivalent; PA, physical activity; PPAQ, pregnancy physical activity questionnaire; PSQI, Pittsburgh sleep quality index; SHS, subjective happiness scale.

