### Harms

Any spontaneously reported adverse events and other unintended effects of trial interventions or health status changes (absolute contraindication for PA) should be immediately reported by the participants, the exercise or the healthcare professionals to the principal researcher.

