### Data collection methods

Data will be collected through online (Google Forms) reliable and validated questionnaires, as well as via IN or ON field test assessments. Training for assessors will be provided to promote data quality. Table 1 includes the description of trial instruments. Data collection forms will be accessed by assessors, principal investigators (PIs) and data analysts. Data will be securely stored and managed following established ethical guidelines. Data from participants who do not complete at least 80% of the scheduled sessions will be considered a loss to follow-up.

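### Contraindications for physical activity are scored as change in point prevalence from a baseline that eligibility sets to zero; counting new onset would include events this metric omits (minor)

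*Protocol article*

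**What the plan says.** All references are to the protocol article.

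- **Outcomes, Table 2.** The last secondary row is a prevalence of pregnancy-related symptoms and health parameters. Its examples include "prevalence of gestational diabetes or hypertension and contraindications for PA". The sources named for the row are "Medical records, pregnancy symptoms inventory and get active questionnaire for pregnancy".
- **Outcomes, Table 2, header of the secondary block.** Every secondary outcome is assessed at week 0 and again at weeks 13 and 14. The header states "Analysis metric: change from baseline".
- **Eligibility criteria for participants.** Inclusion requires "no absolute contraindications to exercise during pregnancy". Exclusion covers "medical conditions contraindicating PA and inability to participate in IN or ON formats".
- **Harms.** "health status changes (absolute contraindication for PA) should be immediately reported" to the principal researcher. The section does not link these reports to the Table 2 row.
- **Data collection methods**, repeated under Statistical methods: "Data from participants who do not complete at least 80% of the scheduled sessions will be considered a loss to follow-up".
- **Data management and Statistical methods.** Intention-to-treat analysis is promised, with a per-protocol analysis alongside it for the comparison of the in-person (IN) and online (ON) arms.

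**The concern.** A change in prevalence is informative when the condition can be present or absent at both time points. Here the entry criteria remove it at the first one. What the trial can learn about this item is whether women develop a contraindication during the 12 weeks, which is an incidence question. Table 2 instead asks who has one at a single late visit, minus a quantity fixed in advance.

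This is the only Table 2 item that records women becoming contraindicated for exercise. If the header is followed, the tabulated outcome can hold fewer events than the trial's own harm reports and medical records. The reader of the results would then see two counts of the same thing that need not agree.

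**Working it through.** The article states no rate, effect or power for this item, so there is no figure to reproduce. The check sets the sections side by side and adds simple arithmetic.

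**1. The baseline term.** Change = follow-up prevalence − baseline prevalence. For absolute contraindications the inclusion criterion gives baseline = 0, apart from any condition arising between the eligibility check and the baseline assessment. So change = follow-up prevalence; for example 5% − 0% = 5%. For other contraindications the result depends on how the exclusion wording is read. It is not limited to absolute ones, but the article does not settle this.

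**2. The between-arm comparison.** (IN follow-up − 0) − (ON follow-up − 0) = IN follow-up − ON follow-up. The zero baseline cancels and adds no bias.

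**3. What the definition counts.** Take three women under the header as written:

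| Course | Week 0 | Weeks 13–14 | Scored as |
|---|---|---|---|
| Never has a contraindication | 0 | 0 | no change |
| Develops one in week 4, resolved by the visit | 0 | 0 | no change |
| Has one at the visit | 0 | 1 | change |

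The second woman had an event that the outcome does not count.

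**4. How much could be left out (assumed values only).** If 5% to 10% of women ever had a contraindication and 0% to 50% of these had resolved by the visit, then point prevalence = ever × (1 − resolved). This runs from 0.05 × 0.5 = 2.5% to 0.10 × 1 = 10%, so between none and half of the cases go uncounted.

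By duration: assume onset uniform over weeks 0 to 12 and a visit uniform between 12 and 14 elapsed weeks (mean 13). For a condition lasting D weeks, with D from 2 to 12, the share still present at the visit is (12 + D − 13)/12:

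- D = 2: 1/12 = 8.3%
- D = 4: 3/12 = 25%
- D = 8: 7/12 = 58.3%

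The article gives neither durations nor rates, so these show only that the undercount could range from nothing to most cases.

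**5. The attendance rule.** Table 1 gives 2 sessions × 12 weeks = 24 sessions. Attending 20 is 83.3%; attending 19 is 79.2%. Missing five sessions, or 5/2 = 2.5 weeks, therefore makes a woman a loss to follow-up. A woman who stops for good after 19 or fewer sessions, that is by about 19/2 = 9.5 weeks, is caught by the rule. Long-lasting conditions are the ones a late visit would still see. If they stop attendance early enough, the rule can remove them.

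**The case against.** The strongest reply is that this is a matter of labelling. Contraindications are one of several examples in a composite secondary row, and the header is shorthand for a mixed block that also holds scales and weight. A condensed article may leave item-level scoring to the full protocol or analysis plan. Medical records are a named source for this very row and can show events between visits, and the Harms section requires new absolute contraindications to be reported at once. Gestational diabetes in the same row raises the same question of prevalence against incidence.

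Much of this stands. It limits the severity, and it means the data need not be lost. It does not remove the point, because the article itself fixes the two time points and the metric, and a prevalence at two visits does not use what the records and reports show in between.

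Three stronger readings are tempting, and the document does not support them.

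- *A before-after test within each arm would show a worsening created by the entry rule.* Statistical methods names paired tests only for continuous variables; categorical data get Pearson's χ² or Fisher's exact test. Even if an exact McNemar test were applied from a zero baseline, two-sided significance needs 6 cases (5 cases: 2 × 0.5⁵ = 0.0625; 6 cases: 2 × 0.5⁶ = 0.031). In an arm of 100 at an assumed 5% prevalence, the chance of 6 or more is about 38%. Each such case would also be a real event after entry.
- *The metric biases the trial towards declaring both formats equally safe.* The shared zero baseline cancels, and the equivalence hypothesis concerns effectiveness. No safety-equivalence conclusion is planned.
- *Transient conditions go unrecorded.* They are uncounted by the outcome as defined, which is a narrower statement.

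**Conclusion.** The point holds at minor severity. As written, the metric for this item has an empty baseline term, certainly for absolute contraindications and arguably for all. It also leaves out any contraindication that resolves before weeks 13–14. Some longer-lasting cases may drop out through the 80% rule as well, if the women concerned stop attending.

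The size of the undercount cannot be derived from the article. Under the assumed values above it lies between none and half of the cases, and it could be larger if most conditions were short. The primary outcomes, the sample size and the validity of the randomised comparison are unaffected.

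The conclusion rests on two assumptions: that the Table 2 header applies to this item as it does to the rest of the block, and that no other document already defines the item as an event.

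**What to change.** For this item only, replace change from baseline in Table 2 with: new-onset contraindication for physical activity (yes/no) at any time from randomisation to the week 13–14 visit. Report it as number and percentage of all women randomised to each arm, with the IN–ON risk difference and 95% CI. Take events from the Harms reports, medical records and the get active questionnaire for pregnancy. State whether the item covers absolute contraindications only or any, and that women below 80% attendance stay in both numerator and denominator, in line with the promised intention-to-treat analysis.

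The cost is one line in Table 2 and a slightly different tabulation of data from sources already named. No visit, instrument, sample size or clinical rule changes. The downside is that the event count may look less favourable than a single-visit prevalence. The interval will also be wide: at an assumed 5% in each arm of 100, the half-width is about 1.96 × √(2 × 0.05 × 0.95/100) = 6 percentage points. The result should be presented as descriptive.
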